#### **9.5. EXPLORATORY ANALYSIS OF EFFICACY CRITERIA**

All statistical tests will be two-sided using  $\alpha=0.05$ . An appropriate pooled center algorithm will be defined prior to unblinding the data. No adjustment for multiple testing will be done since the primary variable and the primary population is well defined.

## **9.6. ANALYSIS OF SAFETY DATA**

The assessment of safety will be based mainly on the frequency of adverse events and on the laboratory data analysis detailed below. Vital signs will also be considered. .

The following analyses will be presented for laboratory data:

- Mean, median and change from baseline in laboratory values will be presented by visit.

## **9.7. ANALYSED POPULATION**

The intent-to-treat population will be used for the primary and secondary analyses. Background data will be summarized for intent-to-treat patients. The per-protocol population will be used for the primary efficacy analysis only. Data from all patients will be listed.

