### **3 STUDY DESIGN**

The study will be a monocentre, randomized, double-blind, crossover, placebo-controlled study in 24 COPD patients (including 4 Drop-out) in order to achieve 20 evaluable patients for the statistical analysis. 'Evaluable' mean eligible COPD patients having met all the inclusion and none of the exclusion criteria, having performed all scheduled clinical visits and with a "good" compliance as defined in section 7.5.

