#### **9.4. ANALYSIS OF EFFICACY CRITERIA**

The primary endpoint is sputum weight after 3 weeks of Tylaxopol– that after 3 weeks of saline treatment which will be analyzed for the Per Protocol Population. Estimated differences will be presented together with 95% confidence intervals (CIs) for the difference and two-sided p-values from a corresponding t-test. This analysis will be repeated for the ITT Population.

Secondary endpoints: The analysis of symptom scores ((CAT, BDI and TDI), ease of sputum production by analog scale, lung function parameter (FVC, FEV1, MEF25, RV, RV/TLC), will use the same methodology as that for the primary endpoint, using the ITT population. The analysis will include Day 1 and week 3 data. In addition acute changes of sputum weight on Day 1 at each treatment arm will be analyzed as described for the primary parameter. Secondary analyses aim to determine the efficacy BP versus placebo to modulate CRP and reducing the symptoms.

Data will be summarized with respect to demographic and baseline characteristics, efficacy observations and measurements, and safety observations and measurements.

Primary and secondary confirmatory analyses will be performed and reported at the end of the double-blind treatment period. A full statistical analysis plan will be produced prior to unblinding the study.

Biomarker profiles (sputum cells, IL-1, IL-6, IL-8), in sputum will be analyzed using an analysis of covariance (ANCOVA) model with covariates of baseline, smoking status and treatment. Estimated treatment differences along with corresponding 95 % CIs will be presented for the treatment comparison.

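### The primary analysis population is not ranked consistently (Per Protocol in 9.4, both ITT and Per Protocol in 9.7), and the only Per-Protocol-like definition depends on a section 7.5 that does not exist

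*Protocol*

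**What the plan says.** **Per Protocol first.** Protocol 9.4 takes the within-patient difference in sputum weight, Tyloxapol minus saline, "which will be analyzed for the Per Protocol Population", and adds: "This analysis will be repeated for the ITT Population". The synopsis and 7.1.1 say the same. Section 2.2 names only Per Protocol and does not mention ITT. Secondary endpoints are assigned to ITT.

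**Both sets.** Section 9.7 opens with "The intent-to-treat population will be used for the primary and secondary analyses". Two sentences later it says: "The per-protocol population will be used for the primary efficacy analysis only". It does not rank them.

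**Multiplicity.** Section 9.5 states: "No adjustment for multiple testing will be done since the primary variable and the primary population is well defined".

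**Definition.** Neither population is defined in so many words. The nearest text is in Section 3, where an evaluable patient must be eligible, must have attended every scheduled clinical visit and must show good "compliance as defined in section 7.5". Section 7 ends at 7.3 in both the table of contents and the body. Section 5.4 provides a compliance check at Visits 3 and 6 but sets no threshold.

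**Safeguards.** Section 9.2 plans a blind review that defines the data sets before code break. Section 9.4 promises a full SAP before unblinding.

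**The concern.** Section 9.7 is the place where a reader looks to learn which set carries the conclusion, and it gives two answers. The argument in 9.5 for making no adjustment depends on there being one.

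If Per Protocol does lead, a second problem follows. Section 1 gives the lack of trials showing possible superiority over saline as a reason for the study. For a superiority comparison, a set selected by attendance and compliance after randomisation is no longer protected by the randomisation. Missed visits and poor compliance can be related to tolerability, to symptoms or to the treatment being taken at the time. Section 4.3 also lists development of an excluded condition as a possible reason for discontinuation; active lung infection is one such condition and could plausibly affect sputum output.

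The Section 3 rule is also stricter than the endpoint needs. Taken as the Per Protocol rule, it would drop a patient who missed only Visit 2 or Visit 5, although both primary weights come from Visits 3 and 6.

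**Working it through.** **1. The passages side by side**

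| Section | Population for the primary endpoint | Ranking |
|---|---|---|
| Synopsis, 7.1.1, 9.4 | Per Protocol, then ITT | ITT is a repeat |
| 2.2 | Per Protocol | ITT not mentioned |
| 9.7, first sentence | ITT | none |
| 9.7, third sentence | Per Protocol | none |
| 9.5 | said to be well defined | not named |

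Four places put Per Protocol first and none puts ITT first. Section 9.7 alone cannot settle the order.

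**2. The plan's own sample size**

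Inputs (synopsis, 9.3, 9.5): difference 1.2 g; SD 1.7 g, read as the SD of the within-patient difference; two-sided α = 0.05; stated N = 20 for 80% power. The power of a paired t-test comes from the noncentral t distribution with n − 1 degrees of freedom and noncentrality (1.2/1.7)·√n.

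- n = 18 (Per Protocol number in the synopsis): 80.6%. This is the smallest n that reaches 80%.
- n = 20 (stated N, and the evaluable target in Section 3): 84.9%.
- n = 24 (recruitment target in Section 3), if all have both weights and the full 1.2 g applies: 91.2%.

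The stated N is adequate on its own inputs, so the sample size is not in dispute.

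**3. Type I error if either set could be declared primary**

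The plan's figures give two pairs of set sizes: 24 recruited with 20 evaluable (Section 3), and 20 allocated with 18 analysed per protocol (synopsis). For each pair, 400,000 trials were simulated with no treatment effect and exclusions unrelated to outcome. A paired t-test was applied to the full set and to the subset, and a trial counted as positive if either test had p < 0.05.

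- 24 and 20: 6.9%.
- 20 and 18: 6.5%.
- Either test alone: 5%.

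These runs give every excluded patient a complete pair of weights. Section 3 calls the four patients drop-outs. Someone who leaves before Visit 6 has no within-patient difference and so enters neither t-test unless values are imputed. If all four were such patients, the two sets would coincide and the error rate would return to 5%.

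**4. What the choice of set could do to the estimate**

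Illustration only: suppose 4 of 24 patients are excluded from Per Protocol, have both weights and gain nothing. The mean over all 24 is then 1.2 × 20/24 = 1.0 g, and power at n = 24 with SD 1.7 g is 78.8%. Nothing in the protocol says that excluded patients would show no effect.

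**The case against.** The strongest reply is that the passages can be reconciled. In 9.7, ITT may serve the primary endpoint as the announced repeat and serve the secondary endpoints, while Per Protocol is confined to the primary endpoint. With 9.4 supplying the order, Per Protocol leads. This reading is plausible and probably what was meant. But 9.7 does not say it, and it leaves the superiority claim on the set that depends on conduct after randomisation. The planned ITT repeat softens that weakness without removing it.

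A reader might infer that the sponsor could claim success on whichever set is significant. The documents do not support that: the blind review requires signed minutes and a confirmed database lock before code break, and the SAP must precede unblinding.

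A reader might also infer that Per Protocol exclusions favour the active product, or that they overstate the effect by 20% (1.2 g against 1.0 g). Neither is shown. In a crossover, excluding a patient removes the data for both treatments, and the 20% needs complete data with no benefit in all four patients.

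Nor does the protocol exclude patients for a treated exacerbation during the study. The exclusions for steroids, antibiotics and hospitalisation concern the four weeks before Visit 1, and 4.3 lists reasons why a patient may discontinue.

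Finally, the link between 'evaluable' and Per Protocol is an inference. Section 3 never equates them, and the numbers differ (20 evaluable, 18 per protocol). It is the only candidate definition in the protocol. A fuller definition could properly sit in the SAP, so missing detail is not the complaint; the reference to a non-existent section is.

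**Conclusion.** The point stands on the text. Section 9.7 gives the primary analysis two populations without ranking them, the premise of 9.5 is therefore not met as written, and the compliance standard in Section 3 points to a section that does not exist. On the most natural reading Per Protocol leads, which is a weak basis for a superiority claim.

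The numerical consequence is modest. Type I error of about 6.5% to 6.9% is an upper figure. It assumes a free choice between the sets, exclusions unrelated to outcome and complete pairs in all excluded patients. With true drop-outs, or with the set fixed at the blind review or in the SAP, the excess shrinks toward zero. The direction and size of any bias from leading with Per Protocol cannot be determined from the protocol.

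**What to change.** Before unblinding:

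1. Name ITT as the single primary population: all randomised patients, analysed as randomised, with sputum weights at Visits 3 and 6. That suits the stated t-test on differences. If patients with only one period are to be included, the t-test will not do; specify instead a mixed model with period and treatment effects.
2. Make Per Protocol a supportive analysis.
3. Use the same sentence in the synopsis, 2.2, 7.1.1, 9.4 and 9.7, so that the statement in 9.5 becomes true.
4. Tie the Per Protocol set to available Visit 3 and Visit 6 weights rather than attendance at every visit, and say whether 'evaluable' in Section 3 means this set.
5. Replace the reference to 7.5 with the actual compliance rule.

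The cost is a change of wording, plus a model specification if one-period patients are admitted. No further patients or measurements are needed. The downside is that the estimate may be slightly less favourable than the Per Protocol one.

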# **10 ETHICAL CONSIDERATIONS AND PATIENT'S CONSENT**

## **10.1. ETHICAL CONSIDERATIONS**

The study will be carried out in accordance with the principles stated in the Declaration of Helsinki, last revised version (see Attachment 23.5) and in accordance with Good Clinical Practice (GCP) and applicable regulatory requirements.

## **10.2. ETHICS COMMITTEES (EC), COMPETENT AUTHORITIES (CA)**

According to the regulatory requirements of the country, the Sponsor will submit the study documentation to the relevant Ethics Committee (EC).

Patients must not be entered into the study until approval of the Ethics Committee and notification of Competent Authorities as defined by local regulatory requirements. All subsequent substantial amendments must be submitted to the Ethics Committee(s) for approval/information and/or to the Competent Authorities according to the local requirements.

The Ethics Committee(s) must also be informed of any serious and unexpected adverse reactions (SUSARs) occurring during the study, which are likely to affect the safety of the volunteers or the conduct of the study.

### **10.3. INFORMED CONSENT**

The investigator must explain to each patient (or legally authorized representative) the nature of the study, its purpose, the procedures involved, the expected duration, the potential risks and benefits involved and any discomfort it may entail. Each patient must be informed that participation in the study is voluntary and that he/she may withdraw from the study at any time and that withdrawal of consent will not affect his/her subsequent medical treatment or relationship with the treating physician.

### **11 INSURANCE**

During the trial an insurance will cover all patient risks and obligations which are necessary for a clinical trial.

### **12 PATIENT DOCUMENTATION AND MONITORING**

#### **12.1. CASE REPORT FORM (CRF)**

CRFs for individual patients will be provided by the study site.

Patients are identified, according to national requirements, solely by the pre-printed CRF number and randomisation number. CRFs are used to record clinical trial data and are an integral part of the study and subsequent reports. The entries, therefore, must be legible and complete. The CRF can be completed by the investigator/authorized persons (mentioned in the centre study personnel identification form). Errors should be lined out but not obliterated and the correction inserted, initialed and dated.

### **13 DRUG ACCOUNTABILITY**

The investigator must maintain accurate and adequate records including dates, batch number, quantities received, individual usage, etc. The investigator must also return to the Sponsor unused supplies giving an exact amount of usage in the study whether completed or terminated. At the time of return to the Sponsor, the investigator must verify that all unused or partially used drug supplies have been returned by the volunteer and that no remaining supplies are in his/her possession.

## **14 ADMINISTRATIVE ISSUES**

### **14.1. RULES FOR AMENDING THE PROTOCOL**

Any change to the protocol, once the final version has been issued, has to be detailed in a protocol amendment. Amendments to the trial are regarded as “substantial” where they are likely to have a significant impact on:

- the safety or physical or mental integrity of the subjects;
- the scientific value of the trial;
- the conduct or management of the trial;
- or the quality or safety of any investigational medicinal product (IMP) used in the trial.

In all cases, an amendment is only to be regarded as “substantial” when one or more of the above criteria is met. Substantial amendments must be submitted to the Competent Authorities (CA) and Ethics Committees concerned for approval. Non-substantial amendments have to be sent for notification to the CA and EC and should be available upon request for inspection at the trial site and/or Sponsor’s premises as appropriate.

All amendments must be numbered, dated and signed. Substantial amendments must be signed at least by the coordinating investigator and the Sponsor/CRO, non-substantial amendments will be signed by the Sponsor and/or CRO and the coordinating investigator, if appropriate.

### **14.2. ARCHIVING**

The investigator must keep the study specific volunteer documentation for at least 10 years after termination of the trial. The investigator should take measures to prevent accidental or premature destruction of the study documents as long as they have to be maintained according to the applicable regulatory requirements and at least until the Sponsor has informed him/her that they no longer need to be retained.

**17            REPORTING AND PUBLICATION**

Any formal presentation or publication of data from this trial will be considered as a joint publication by the investigator(s) and appropriate benepharma personnel. Authorship will be determined by mutual agreement.

**18            FINANCIALS**

Financials are listed in a separate document.

**19            CONTINUATION SUPPLY**

After completion of the trial no continuation supplies will be made available for the patients. If a treatment is necessary the investigator will treat the patients according to the science based guidelines. Alternatively, the investigator will inform the patient's general practitioner (GP) at the end of the trial period. The patient will then be advised to visit his GP directly.

